**Fig 1 pone.0300898.g001:**
[figure not shown]
The schedule of enrolment, interventions, and assessments of SPIRIT 2013.

#### Blinding

The work of sequencing, randomisation, recruitment and allocation of the senior centres to each group (experimental or control) will be completed by research staff not involved in the evaluations or interventions of each group, which will avoid possible biases in the study.

The participants will also be blinded on the hypothesis and expectations of the study. In order to minimise any contamination between groups, the evaluation process will be carried out by external research staff who will carry out the measurements, previously educated and trained; with the aim of avoiding subjective biases in the process, as they will be unaware of the intervention group to which each elderly centre is assigned, so that the clinical trial will have a masking of blind evaluation by third parties. In addition, the researchers responsible for the statistical analysis of the study will be blinded, with the intention of increasing the rigour of the study process, thus increasing the scientific quality.

#### Sample size

The sample size has been estimated using Epidat 4.2. A one-sided approach has been assumed with a confidence level of 95% and a statistical power of 80%. It has been decided to take equal sizes in the two groups (i.e. R = n2/n1) and the Yates correction will not be applied. The sample size calculation was based on the results of a similar RCT, specifically the study conducted by Fernández et al. in 2018 [16] which compared the outcomes of a traditional cognitive stimulation intervention versus an intervention based on everyday cognition. The primary variable chosen in both studies was everyday cognition. The study found that the experimental group (those who received everyday cognition training) demonstrated an improvement of 2.57 points in the primary variable, while the control group (those who received traditional cognitive stimulation) only demonstrated an improvement of 0.39 points. With an expected population loss of 20%, the final sample size was n = 99 participants, with 50 in the experimental group and 49 in the control group.

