### Data analysis

To test the normal distribution of data, a histogram will be used. Variables that have a normal distribution shall be defined by the mean and standard deviation, while variables that do not follow a normal distribution shall be defined by the median and the interquartile range. The effects of the intervention on primary outcomes (everyday cognition and cognitive function) and secondary outcomes (functionality, emotional state, and fragility) will be examined through a two-way analysis of covariance (ANCOVA), with the intervention group (control or experimental) included as a fixed factor. The differences between initial results and those after intervention, as both the dependent variable and covariates, will include intervening study variables such as age, gender, education level, marital status and occupation. The difference in means will be calculated using Cohen’s d to evaluate effect size. Group differences in intervening variables will be analyzed using independent samples t-tests for continuous variables (e.g., age). The chi-square test will be used to investigate group differences in categorical variables (e.g. gender). Significant values will be considered for p-values less than 0.05, with a 95% confidence interval. IBM SPSS Statistics software version 28.0.1 will be used for statistical analysis”.

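### The sample size is set for a one-sided 5% test at 80% power, but the analysis described reads as two-sided at 5%, for which power is about 70% on the protocol's own inputs

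*Protocol article*

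**What the plan says.** The Sample size section of the protocol article gives the basis of the calculation: "A one-sided approach has been assumed with a confidence level of 95% and a statistical power of 80" per cent. The allocation is equal. The effect comes from an earlier trial with everyday cognition as its primary variable: the trained group "demonstrated an improvement of 2.57 points in the primary variable", and the comparison group "only demonstrated an improvement of 0.39 points". The result is "With an expected population loss of 20%, the final sample size was n = 99 participants, with 50 in the experimental group and 49 in the" (comparison arm). No standard deviation is reported.

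The Data analysis section says that the primary and secondary outcomes "will be examined through a two-way analysis of covariance (ANCOVA), with the intervention group (control or experimental) included as a fixed factor". Its decision rule is "Significant values will be considered for p-values less than 0.05, with a 95% confidence interval". It mentions no one-sided test, no one-sided confidence bound, no 90% interval and no halving of the p-value. It also does not say that the tests are two-sided.

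**The concern.** The two sections appear to describe different tests. The sample size puts the whole 5% in one tail. The analysis uses an F test, which counts departures in either direction, together with a 95% interval, which leaves 2.5% in each tail. A one-sided 5% test would pair with a one-sided 95% bound or a two-sided 90% interval.

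If the analysis is run as it reads, the chance of missing the assumed effect is about 30%, not the 20% that the sample size section implies. A reader who relies on the stated 80% would give a null result more weight than the design supports. If the point stays open, sidedness could also be settled after the results are known.

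**Working it through.** **Inputs from the Sample size section:** one-sided α = 0.05; power 80%; equal arms; difference 2.57 − 0.39 = 2.18 points; loss 20%; N = 99.

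**Inputs from the Data analysis section:** ANCOVA F test; p < 0.05; 95% interval.

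**Normal quantiles:** z(0.95) = 1.645, z(0.80) = 0.842, z(0.975) = 1.960.

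**1. Can N = 99 be reproduced?** Not forward, because no standard deviation is given. It can only be solved backwards, from SD = 2.18 / [(1.645 + 0.842) × √(2/n)].
- If 99 was reached by dividing by 0.8, the evaluable total is 99 × 0.8 = 79.2, or n = 39.6 per arm. The implied SD is 3.90.
- If 99 was reached by multiplying by 1.2, the evaluable total is 99 / 1.2 = 82.5, or n = 41.25 per arm. The implied SD is 3.98.

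The stated one-sided inputs and N = 99 are therefore compatible with a change-score SD of about 3.9 to 4.0. A two-sided calculation would also reach 99 if the SD were about 3.46 to 3.53. The figure 99 alone does not show which was used; the text does.

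**2. Two-sided power at the same n and effect.** If n gives 80% power one-sided at 5%, the standardised effect (difference divided by its standard error) is 1.645 + 0.842 = 2.487. Two-sided power at 5% is then, ignoring the negligible opposite tail:

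Φ(1.645 + 0.842 − 1.960) = Φ(0.527) = 0.70.

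The standard deviation cancels, so its absence does not affect this result. The noncentral t distribution with 40 or 41 per arm gives 0.698.

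**3. Sample needed to keep 80% two-sided.** The inflation factor is [(1.960 + 0.842) / (1.645 + 0.842)]² = 1.27.
- 39.6 × 1.27 = 50.3 per arm, about 101 evaluable in total; divided by 0.8, about 126 enrolled.
- 41.25 × 1.27 = 52.4 per arm, about 105 evaluable in total; multiplied by 1.2, about 126 enrolled.

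**4. Sensitivity to loss.** If nobody were lost (49.5 per arm), two-sided power would be about 79% at SD 3.90 and about 78% at SD 3.98. The protocol's 80% is itself the power after the 20% loss, so 70% is the like-for-like comparison.

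**The case against.** The strongest reply is that the contradiction is inferred. The Data analysis section never says two-sided, a threshold of 0.05 also fits a one-sided 5% test, and the Aim section states a directional hypothesis. That stands as a limit on the claim. A reader might infer that the 80% belongs to a test that will certainly not be run; the article does not support that, because it leaves the direction of the final test unstated. The F test and the 95% interval make two-sided the ordinary reading, and nothing in that section carries the one-sided assumption through.

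A second reply is that 70% is conditional. Covariates explaining about 21% of the outcome variance (1 − 1/1.27) would offset the loss. That is possible, but the covariates listed by name are demographic, the article gives no figure for what they explain, and its own calculation takes no credit for them. In the other direction, the Randomisation section allocates eleven whole groups, which would lower power further; that is a separate matter. The remark that "the Yates correction will not be applied" belongs to a calculation for proportions, so the method behind 99 is uncertain. The stated sidedness, α and power are enough for the 70%.

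A reader might also infer that a one-sided test is wrong here because the comparator is active and could do better on the MoCA, or because one-sided 5% doubles the conventional 2.5%. The documents do not support calling that an error. The sample size rests on everyday cognition alone, so the MoCA argument does not bear on it, and the rest is convention.

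**Conclusion.** The mismatch is real and should be corrected. The stated 80% applies to a one-sided 5% test, while the analysis as ordinarily read is two-sided at 5%, with power of about 70%. That figure rests on the sizing having been one-sided as stated, the planned 20% loss occurring, participants being independent, and no gain from covariate adjustment. It does not depend on the unreported standard deviation. If the analysis is two-sided, its nominal 5% error rate is not affected by this mismatch and the estimates do not change; what is overstated is the planned power.

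**What to change.** In Data analysis, state that the primary tests are two-sided at 5%, in line with the 95% interval. In Sample size, keep the record that N = 99 was derived one-sided, because the 70% follows from that basis and could not be traced without it. Add that the planned power for the two-sided test is about 70% on the same inputs, before any loss from allocating whole groups. Report the standard deviation used, so that 99 can be checked.

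This takes a few sentences and no change to enrolment. The cost is a less favourable stated power. If the sponsor wished instead to keep 80% two-sided on these assumptions, about 126 would have to be enrolled, still without any allowance for whole-group allocation.

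### The sample size of 99 is described with a proportions-only setting and no SD, so it is not a valid or reproducible calculation for the planned comparison of mean score changes

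*Protocol article*

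**What the plan says.** The Sample size section lists the settings entered in Epidat 4.2. The first is "A one-sided approach has been assumed with a confidence level of 95% and a statistical power of 80" (per cent). The next are "equal sizes in the two groups (i.e. R = n2/n1) and the Yates correction will not be applied".

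For the effect it relies on one earlier trial: "The sample size calculation was based on the results of a similar RCT". In that trial the experimental arm "demonstrated an improvement of 2.57 points in the primary variable", and the control arm "only demonstrated an improvement of 0.39 points". It concludes: "With an expected population loss of 20%, the final sample size was n = 99 participants". The stated split is 50 experimental to 49 control. No SD, standardised effect or pair of proportions appears.

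The Description of the variables section makes the primary variables two test scores, PECC and MoCA. The Data analysis section plans an ANCOVA with group as a fixed factor and describes the outcome as follows: "The differences between initial results and those after intervention, as both the dependent variable and covariates". It declares significance at p below 0.05 with a 95% confidence interval. Chi-square tests appear only for group differences in categorical intervening variables. The Randomisation section allocates the eleven centre groups, not individuals.

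**The concern.** Whether to apply the Yates correction is a choice that arises only when two proportions are compared in a 2x2 table. A two-mean calculation has no such option. What it does need, besides the difference, is the SD of the outcome, and that is the one input missing from an otherwise complete list. The protocol defines no responder and no binary primary outcome, so the setting described does not belong to the endpoint or to the test.

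This paragraph is the only support for the trial's size and for its 80% power. If the calculation does not match the analysis, the real power could lie well above or well below 80%, and a reader cannot tell which.

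**Working it through.** **Inputs from the protocol.** One-sided alpha 0.05, power 80%, ratio 1:1, mean gains 2.57 and 0.39, loss 20%, total 99 (50 + 49). The difference is 2.57 − 0.39 = 2.18 points. The SD of change is not given; every SD below is an assumption.

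**Step 1: the loss allowance.** 99 × 0.8 = 79.2, so about 79 completers. In reverse, 79 / 0.8 = 98.75, rounded up to 99. By arm, 40 / 0.8 = 50 and 39 / 0.8 = 48.75, rounded up to 49. The stated total and split therefore agree with a correct allowance for 20% loss.

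**Step 2: can 99 be reproduced as a comparison of means?** The normal-approximation formula is n per arm = 2 (z_α + z_β)² (SD / difference)², with z_α = 1.645 and z_β = 0.842. Without an SD it gives no number. Solved backwards, it gives 99 when the SD is about 3.9: 2 × (2.486)² × (3.9 / 2.18)² = 39.6 per arm, or 79.1 in total, and 79.1 / 0.8 = 98.9. With the noncentral t distribution at 40 v 39, the SD that gives exactly 80% is 3.86, a standardised difference of 2.18 / 3.86 = 0.565.

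**Step 3: can 99 be reproduced as a comparison of proportions?** Reading the gains as 2.57% and 0.39%, one-sided, without Yates, gives 379 per arm, or 758 before loss. That is not 99. The protocol offers no other reading of these figures as proportions.

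**Step 4: power at 40 v 39 completers.** Noncentrality = 2.18 / (SD × √(1/40 + 1/39)), 77 degrees of freedom, alpha 0.05, participants treated as independent.

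| Assumed SD of PECC change | One-sided power | Two-sided power |
|---|---|---|
| 3 | 94% | 89% |
| 3.86 | 80% | 70% |
| 3.9 | 79% | 69% |
| 4 | 78% | 67% |
| 5 | 61% | 48% |
| 6 | 48% | 36% |

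The two-sided column matters because a group test in ANCOVA at p below 0.05, reported with a 95% confidence interval, is two-sided unless stated otherwise.

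**Step 5: allocation of whole groups.** Eleven groups for 99 participants average 99 / 11 = 9 each. The design effect is 1 + (9 − 1) × ICC, which is 1.08, 1.16 and 1.40 for assumed ICCs of 0.01, 0.02 and 0.05. The protocol gives no ICC. For any positive ICC the powers in the table are too high.

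**The case against.** The strongest reply is that this is a reporting slip. The article says the correction is not applied, so the clause changes no number and may be left over from a software menu. The effect is stated in points, which suits a comparison of means. An SD near 3.9 reproduces 99, and the prior trial that is named could have supplied it. A journal article need not repeat every input.

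Much of this stands. A reader might infer that a proportions formula was actually used. The documents do not support that: the direct percentage reading does not return 99, while a two-mean calculation with an undisclosed SD does. A reader might also suspect that the 20% loss was applied wrongly. Step 1 shows that 99, 50 and 49 all follow from dividing by 0.8. Nor is it shown that the trial is underpowered, since at an SD below 3.86 the one-sided power exceeds 80%.

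What does not stand is that the paragraph is adequate as written. It fixes and justifies the size here, includes a setting that cannot apply to the endpoint, and leaves out the one quantity on which the result turns. That goes beyond condensed detail, because the stated specification and the stated analysis are incompatible.

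**Conclusion.** The point holds in this form: as described, the calculation is neither valid nor reproducible for the planned ANCOVA on score change. The claim of 80% power rests on an unstated SD of PECC change of at most about 3.86. For assumed SDs from 3 to 6, one-sided power runs from 94% down to 48%. At SD 3.9, close to the value that would explain 99, the two-sided test implied by the Data analysis section has about 69%. These figures assume 79 completers, a true difference of 2.18 points, independent participants and no gain in precision from covariates. The direction of any error in the stated one-sided power is unknown, because the SD is unknown. The paragraph should be corrected; the number 99 itself has not been shown to be miscalculated.

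**What to change.** Delete the Yates clause. State the SD of PECC change and its source, and recompute with a two-mean formula. Use the same sidedness in the calculation and in the planned test. Account for the allocation of whole groups with a stated, justified ICC. Keep the division by 0.80 for loss. Then report the power, or the detectable PECC difference, that 99 enrolled and about 79 completers give.

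The cost is one amended paragraph. The drawback is that the stated power may become less favourable. Whether 99 is still enough can be judged only once the SD and the ICC are on record.

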#### Randomisation

Participants voluntarily enroll in one of the eleven groups that belong to different senior centers to receive one of two types of cognitive intervention. In order to ensure the greatest fairness among the different groups, a maximum of 15 and a minimum of 5 participants per group were established. Following recruitment, randomization will be carried out through simple allocation of each group belonging to each senior group by using the Epidat 4.2 program. The eleven intervention groups will be allocated to either the experimental or control group as detailed in Fig 1 of the SPIRIT 2013 registration, interventions and assessments program.

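### The 80% power claimed for n = 99 comes from participant-level inputs, but eleven intact groups are randomised, so the design is not shown to have that power

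*Protocol article*

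**What the plan says.** The Sample size section of the protocol article sets the operating characteristics: "A one-sided approach has been assumed with a confidence level of 95% and a statistical power of 80" percent. On allocation it adds "It has been decided to take equal sizes in the two groups". The effect comes from an earlier similar trial, in which the everyday-cognition arm "demonstrated an improvement of 2.57 points in the primary variable" and the traditional-stimulation arm improved by 0.39. After an expected 20% loss, "the final sample size was n = 99 participants, with 50 in the experimental group and 49 in the control group". The section also says that the Yates correction is not applied. It states no SD, formula, intracluster correlation, design effect or number of groups.

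The Randomisation section describes another unit. People first enrol in one of eleven groups, for which "a maximum of 15 and a minimum of 5 participants per group were established". Then "randomization will be carried out through simple allocation of each group belonging to each senior group by using the Epidat 4.2 program", and "The eleven intervention groups will be allocated to either the experimental or control group". The Blinding section agrees: "allocation of the senior centres to each group (experimental or control) will be completed by research staff not involved in the evaluations". The evaluation plan speaks of allocating subjects, which fits individual randomisation, but the two sections that describe the mechanism allocate groups.

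**The concern.** Members of a group choose the same centre before allocation and then share a room and 25 weekly sessions. Their outcomes may be correlated, and the arm comparison then carries between-group variance that a formula for independent individuals leaves out. There are also only eleven allocated units, so a group-level comparison has few degrees of freedom.

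The power figure is finished and published. It is not a detail left for an analysis plan. If it belongs to a different design, a null result could be read as good evidence of no difference from a trial with 80% power, when its chance of detecting the planned difference may be lower.

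**Working it through.** **Inputs from the protocol article.** Difference 2.57 − 0.39 = 2.18 points; one-sided α 0.05; power 80%; loss 20%; N = 99; 11 groups.

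**Inputs that are assumptions.** A two-means formula for independent individuals; an ICC of 0.01, 0.05 or 0.10; balanced arms; equal group sizes.

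**1. The plan's own figure.** Without an SD, 99 cannot be reproduced. It can only be back-solved.
- Evaluable: 99 × 0.8 = 79.2, taken as 79, or 39.5 per arm. This fits the stated split, since 39/0.8 rounds up to 49 and 40/0.8 = 50.
- SD = 2.18 / [(1.645 + 0.842) × √(2/39.5)] = 2.18 / (2.486 × 0.225) = 3.90 (unrounded z-values sum to 2.486).
- d = 2.18 / 3.90 = 0.56.

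Under that formula the 99 is used up by the individual-level calculation and the 20% loss. Nothing is left for clustering.

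**2. Design effect.** Evaluable group size m = 79/11 = 7.18. DE = 1 + (m − 1) × ICC. Effective sample size = 79/DE. Noncentrality = 2.486/√DE.

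**3. Power.** The normal approximation is Φ(noncentrality − 1.645). The group-level version uses a noncentral t on 11 − 2 = 9 df (one-sided critical value 1.833).

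| ICC (assumed) | DE | Effective N | Noncentrality | One-sided, normal | One-sided, t on 9 df |
|---|---|---|---|---|---|
| 0 | 1.00 | 79 | 2.486 | 80% | 74% |
| 0.01 | 1.06 | 74 | 2.41 | 78% | 72% |
| 0.05 | 1.31 | 60 | 2.17 | 70% | 64% |
| 0.10 | 1.62 | 49 | 1.95 | 62% | 56% |

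**4. Sidedness.** The Data analysis section declares significance at p < 0.05 with a 95% confidence interval. If that is read as two-sided, which is an inference, power on 9 df (critical value 2.262) is about 58%, 49% and 42% at ICC 0.01, 0.05 and 0.10.

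**5. Balance.** Simple allocation of 11 units does not guarantee a 6/5 split. Under independent fair allocation, the chance of 7/4 or worse is 1 − 2 × C(11,5)/2¹¹ = 1 − 924/2048 = 55%. With 80 evaluable participants and ICC 0.05, a 7/4 split gives about 67% (normal) or 61% (9 df). Unequal group sizes have a smaller effect: at ICC 0.05, a coefficient of variation of 0.3 in group size raises the design effect from 1.31 to 1.35.

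**6. Full retention.** With all 99 evaluable (9 per group) and ICC 0.01, DE = 1.08 and one-sided power is about 85% (normal) or 79.5% (9 df). At ICC 0.05, DE = 1.40 and power is about 76% or 70%.

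**The case against.** The strongest reply is that the size of the loss is not in the document.

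- **The d of 0.56 is not the plan's.** The article states neither d nor SD. The Yates correction belongs to a comparison of proportions. If a proportions routine produced the 99, the back-solved SD and every power figure above lose their basis. This stands, so the figures can only illustrate.
- **The 9 df are imposed.** The article plans a participant-level ANCOVA. At ICC 0, an individual-level test on 77 df has about 79% power, so the 74% in the table comes only from the group-level reference distribution. This stands, and it is why both versions are shown. The normal approximation, without that penalty, still falls below 80% at every non-zero ICC considered.
- **The participant-level ANCOVA would keep its power.** If no term for group is added, it does so only by treating correlated people as independent. At ICC 0.05 the true two-sided error of a nominal 5% test would be about 8.7% (normal approximation). That is a separate matter and does not rescue the power claim.
- **Covariates may help.** Adjustment could reduce residual and between-group variance. No credit is given for this, because the document offers nothing to quantify it.

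A reader might infer that power is certainly far below 80%. The documents do not support that: at ICC 0.01 the normal approximation leaves 78%, and full retention could roughly restore 80%. A reader might also infer that the plan fixes a two-sided test or contains an arithmetical slip. It never says two-sided, and without an SD no slip can be shown.

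**Conclusion.** The mismatch rests on the text alone: groups are allocated, yet power is stated from individual-level inputs with no clustering allowance. The 80% is therefore unsupported for this design.

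How far true power falls short depends on quantities that the document does not give. Under the labelled assumptions, the one-sided shortfall from 80% is about 2 to 18 percentage points by normal approximation and about 8 to 24 points on 9 df, for ICC 0.01 to 0.10. An uneven split of groups or uneven group sizes would lower power further. The Yates remark changes no number, since the correction is not applied, but it leaves the formula unidentified.

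**What to change.** Keep n = 99. In the Sample size section, replace the 80% claim with the power, or the detectable difference, for eleven randomised groups. State:

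- the SD and the formula used;
- an ICC range, such as 0.01 to 0.10, labelled as an assumption;
- the group size, about 9 enrolled (99/11) and about 7 evaluable (79/11), with the evaluable size used in the design effect;
- the resulting design effect and the 9 between-group df;
- whether the quoted power is one-sided or two-sided.

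Remove the Yates statement, or name the formula it belongs to.

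The cost is one rewritten paragraph and a less favourable power figure. No additional enrolment is needed.
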